#### **1.1.1.1 Skin Lesions**

Visible cutaneous lesions must be measured clinically. Assessment of skin lesions must be performed within close proximity ( $\pm 7$  days) of any protocol-specified radiographic assessments for Treatment and Follow-up Phases.

### **6.4.3.2 Definition of Measurable/Non-measurable Lesions**

#### ***Measurable Lesions:***

Measurable lesions are lesions with clear borders that can be accurately measured in 2 dimensions with the following criteria:

- All measurements should be taken and recorded in centimeters,
- At Baseline the longest diameter and the longest perpendicular diameter must both be greater than or equal to 1.0 cm,
- For CT evaluations, the above definitions assume 5 mm contiguous slices. If slice thickness is greater than 5 mm, the above dimensions double,
- Cutaneous lesions should be photographed using a standard technique at each assessment point to document the clinical response.

#### ***Non-Measurable Lesions:***

- Non-measurable lesions at baseline are all other lesions. These include small lesions (either or both diameter(s)  $<1.0$  cm), bone lesions, leptomeningeal disease, ascites, pleural or pericardial effusions, inflammatory breast disease, lymphangitis cutis/pulmonis, or cystic lesions.

- Ideally, the same method of assessment and the same technique should be used to characterize each identified and reported lesion at baseline and during follow-up. The reader will determine the technical adequacy should the technique/modality change.
- Superficial and palpable-only lesions will be non-measurable for the radiologic portion of the independent review. These lesions will be considered as non-measurable during the IRC assessment unless there are no suitable radiographically measurable lesions. For this clinical assessment, cutaneous lesions should be photographed by a standard technique at each assessment point to document the clinical response. Copies of other imaging assessments, such as chest x-ray or ultrasound, which are not considered measurable for the radiologic assessment but measurable for the clinical assessment, will be kept centrally to document evidence of clinical response.

All measurable and non-measurable lesions should be assessed at Screening and at the defined TA time points (see Table 6.1). Extra assessments may be performed, as clinically indicated, if there is a suspicion of progression.

#### **1.1.1.2 Definition of Index/Non-index Lesions**

Measurable lesions, up to a maximum of 5 lesions per organ and 10 lesions in total, should be identified as index lesions to be measured and recorded on the CRF at Screening. The index lesions should be representative of all involved organs. In addition, index lesions must be selected based on their size (e.g., lesions with the longest diameters), their suitability for accurate repeat assessment by imaging techniques, and how representative they are of the subject's tumor burden. At Screening, a Sum of the Products of Diameters (SPD) for all index lesions will be calculated and considered the baseline SPD. The baseline sum will be used as the reference point to determine the objective tumor response of the index lesions at TA.

Measurable lesions, other than index lesions, and all sites of non-measurable disease, will be identified as non-index lesions. Non-index lesions will be recorded on the CRF and will be evaluated at the same assessment time points as the index lesions. In subsequent assessments, non-index lesions will be recorded as complete response, stable or progression.

#### **Calculation of Sum of Product of Diameters (SPD)**

SPD is an estimation of tumor burden. The 2 greatest perpendicular diameters are used to estimate the size of each tumor lesion. The SPD is calculated as the sum of the product of the diameters for index tumor lesions. Several variations of the SPD are identified for the purpose of classification of tumor responses.

SPD at Baseline: The sum of the product of the diameters for all index lesions identified at baseline prior to treatment on Day 1.

SPD at TA: For every on-study TA collected per protocol Section 6.1 or as clinically indicated, the SPD at TA will be calculated using tumor imaging scans.

SPD at Nadir: For tumors that are assessed more than one time after baseline, the lowest value of the SPD (SPD Baseline or SPD at TA) is used to classify subsequent TAs for each subject.

#### **6.4.3.3 Definition of Tumor Response Using irRC**

As stated in Section 4.1.2.1, when using the ir-response criteria, subjects are allowed to continue to receive study therapy despite radiologic evidence of progressive disease in index lesions, provided this is not accompanied by rapid clinical deterioration.

The SPD at TA using the irRC for progressive disease incorporates the contribution of new measurable lesions. Each net percentage change in tumor burden per assessment using irRC accounts for the size and growth kinetics of both old and new lesions as they appear. In this study the irRC as defined by the investigator will serve for basis of key endpoints and guide clinical care.

#### **Definition of Index Lesions Response using irRC**

- irComplete Response (irCR): Complete disappearance of all index lesions. This category encompasses exactly the same subjects as “CR” by the mWHO criteria.
- irPartial Response (irPR): Decrease, relative to baseline, of 50% or greater in the sum of the products of the 2 largest perpendicular diameters of all index and all new measurable lesions (ie, Percentage Change in Tumor Burden). Note: the appearance of new measurable lesions is factored into the overall tumor burden, but does not automatically qualify as progressive disease until the SPD increases by  $\geq 25\%$  when compared to SPD at nadir.
- irStable Disease (irSD): Does not meet criteria for irCR or irPR, in the absence of progressive disease.
- irProgressive Disease (irPD): At least 25% increase Percentage Change in Tumor Burden (i.e., taking sum of the products of all index lesions and any new lesions) when compared to SPD at nadir.

#### **Definition of Non-Index Lesions Response using irRC**

- irComplete Response (irCR): Complete disappearance of all non-index lesions. This category encompasses exactly the same subjects as “CR” by the mWHO criteria.
- irPartial Response (irPR) or irStable Disease (irSD): non-index lesion(s) are not considered in the definition of PR, these terms do not apply.
- irProgressive Disease (irPD): Increases in number or size of non-index lesion(s) does not constitute progressive disease unless/until the Percentage Change in Tumor Burden increases by 25% (ie, the SPD at nadir of the index lesions increases by the required amount).

#### **Impact of New Lesions on irRC**

New lesions alone do not qualify as progressive disease. However their contribution to total tumor burden is included in the SPD which in turn feeds into the irRC for tumor response. Therefore, new non-measurable lesions will not discontinue any subject from the study.

***Definition of Overall Response Using irRC Will Be Based on the Following Criteria:***

- Immune-related Complete Response (irCR): Complete disappearance of all tumor lesions (index and non-index together with no new measurable/unmeasurable lesions) for at least 4 weeks from the date of documentation of irCR.
- Immune-related Partial Response (irPR): The sum of the products of the 2 largest perpendicular diameters of all index lesions is measured and captured as the SPD baseline. At each subsequent TA, the sum of the products of the 2 largest perpendicular diameters of all index lesions and of new measurable lesions are added together to provide the Immune Response Sum of the Product of the Diameters (irSPD). A decrease, relative to baseline of the irSPD of 50% or greater is considered an irPR. It must be confirmed no less than 4 weeks from the first irPR.
- Immune-related Stable Disease (irSD): irSD is defined as the failure to meet criteria for immune complete response or immune partial response, in the absence of progressive disease.
- Immune-related Progressive Disease (irPD): Unless the subject is rapidly deteriorating, a confirmatory scan not less than 4 weeks since the prior scan should be performed to confirm PD. Any of the following will constitute progressive disease:
  - At least 25% increase in the SPD of all index lesions over nadir SPD calculated for these lesions.
  - At least a 25% increase in the SPD of all index lesions and new measurable lesions (irSPD) over the nadir SPD calculated for the index lesions.

Immune-related clinical activity (irCR, irPR or irSD) relative to baseline can be recorded at any time, including after confirmed irPD, provided that the patient has not received alternative non-ipilimumab anticancer therapy.

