**Table 6.4.1.6: irRC Definitions**

| Index Lesion Definition | Non-Index Lesion Definition | New Measurable Lesions | New Unmeasurable Lesion | % Change in Tumor Burden (including measurable new lesions when present) | Overall irRC Response |
|---------------------------------------|-------------------------------------------|--------------------------------------|---------------------------------------|----------------------------------------------------------------------------------------|-------------------------------------|
| Complete Response       | Complete Response           | No                     | No                      | -100%                                                                    | irCR                  |
| Partial Response        | Any                         | Any                    | Any                     | ≥ -50%                                                                   | irPR                  |
| Response                |                                           |                                      |                                       | < -50% to < +25%                                                   | irSD                  |

Table 6.4.1.6: *irRC Definitions*

| Index Lesion Definition | Non-Index Lesion Definition | New Measurable Lesions | New Unmeasurable Lesion | % Change in Tumor Burden
(including measurable new lesions when present) | Overall irRC Response |
|--------------------------------|------------------------------------|-------------------------------|--------------------------------|-------------------------------------------------------------------------------------|------------------------------|
|                                |                                    |                               |                                | $\geq +25\%$                                                                        | irPD                  |

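### The second irPD criterion compares index plus new lesions with an index-only nadir, so some patients whose disease has not grown can be classed as progressing

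*Combined protocol and SAP*

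**What the plan says.** Under the definition of overall response in Section 6.4.3.3, two criteria for irPD are listed after the words "Any of the following will constitute progressive disease", so either one is enough:

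- First criterion: "At least 25% increase in the SPD of all index lesions over nadir SPD calculated for these lesions". This compares index lesions with index lesions.
- Second criterion, again as a minimum: "25% increase in the SPD of all index lesions and new measurable lesions (irSPD) over the nadir SPD calculated for the index lesions". This compares index plus new lesions with index lesions only.

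Partial response uses a different reference: "A decrease, relative to baseline of the irSPD of 50% or greater is considered an irPR". It needs confirmation at least 4 weeks later.

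Two other places support an index-only nadir:

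- The SPD calculation paragraph: "The SPD is calculated as the sum of the product of the diameters for index tumor lesions".
- The non-index lesion paragraph, which ties progression to the point where "the SPD at nadir of the index lesions increases by the required amount".

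Other wording is looser. The opening of Section 6.4.3.3 says that SPD at an assessment takes in new measurable lesions when progression is judged, and adds: "Each net percentage change in tumor burden per assessment using irRC accounts for the size and growth kinetics of both old and new lesions". The index-lesion definitions compare index plus new lesions with SPD at nadir and do not limit that nadir to index lesions. The SPD paragraph defines nadir as the lowest of the baseline and assessment values, for use at later assessments.

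Table 6.4.1.6 puts all cut-offs in one column, headed as percentage "Change in Tumor Burden (including measurable new lesions when present", and names no reference value.

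**The concern.** A percentage change is interpretable only if both terms measure the same thing. Here, a new lesion already present when the index lesions reached their nadir is missing from the reference and present in every later numerator. It is therefore counted as growth at each later scan even if it never changes size.

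The patients exposed are those with shrinking index lesions and new lesions. Section 1.3.6.2 lists response in the presence of new lesions among the recognised patterns under ipilimumab, and the paragraph on the impact of new lesions says that they are not progression by themselves. The second criterion sits badly with both.

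irPFS (Section 8.3.2.2) and irDoR (Section 8.3.2.1) both end at progression per irRC or death, so the date given by this rule goes straight into them. The plan also gives no rule for an assessment that meets irPR against baseline and irPD against nadir together.

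**Working it through.** **Inputs.** The irPD and irPR criteria come from the overall-response definition in Section 6.4.3.3, and the nadir rule from the SPD calculation paragraph. Lesion sizes are assumptions for illustration, with baseline index SPD = 100. The plan states no figure on this point to reproduce.

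**Formulae.** Let I be the index SPD and N the SPD of new measurable lesions at an assessment, so irSPD = I + N.

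- Change from baseline = (I + N)/100 - 1. irPR if -50% or lower.
- Written second criterion = (I + N)/(lowest earlier index SPD) - 1. irPD if +25% or higher.
- Like-for-like version = (I + N)/(lowest earlier irSPD) - 1.

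**First post-baseline assessment.** The only earlier value is the baseline, so both versions use 100. For 60 + 20: 80/100 - 1 = -20%. For 30 + 15: 45/100 - 1 = -55%, irPR. The mismatch cannot act yet.

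**Second assessment.**

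| Index + new, first then second assessment | From baseline | Written second criterion | Like for like |
|---|---|---|---|
| 60+20, then 60+20 | -20% | 80/60 - 1 = +33.3%, irPD | 80/80 - 1 = 0% |
| 30+15, then 30+15 | -55%, irPR confirmed | 45/30 - 1 = +50.0%, irPD | 45/45 - 1 = 0% |
| 60+30, then 60+20 | -20% | 80/60 - 1 = +33.3%, irPD | 80/90 - 1 = -11.1% |
| 0+10, then 0+10 | -90% | index nadir 0, ratio undefined | 10/10 - 1 = 0% |
| 60+10, then 60+10 | -30% | 70/60 - 1 = +16.7%, not irPD | 70/70 - 1 = 0% |
| 60+0, then 60+0 | -40% | 60/60 - 1 = 0%, not irPD | 60/60 - 1 = 0% |
| 100+20, then 100+20 | +20% | 120/100 - 1 = +20%, not irPD | 120/100 - 1 = +20%, not irPD |

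In the first two rows the index-only criterion is not met (60/60 and 30/30 are both 0% change). The second criterion alone produces the irPD.

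**When it acts.** For unchanged disease with I at the index nadir, (I + N)/I - 1 >= 0.25 reduces to N >= 0.25 x I. If the index lesions have never fallen below baseline, both references are the baseline and the two versions agree (100 + 25 is +25%, irPD under both).

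**Confirmation.** A third identical scan of 60 + 20 gives 80/60 - 1 = +33.3% again, so a confirmatory scan confirms the false progression.

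**Effect on dates.** In the 30 + 15 case, response starts at Week 12. If irPD is dated at the next scheduled scan, irDoR is 18 - 12 = 6 weeks on the Section 4.1.2 schedule, or 20 - 12 = 8 weeks on the schedule in the notes to the Section 6.1 chart, with no tumour growth.

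**The case against.** **The documents also contain the like-for-like reading.** If SPD at an assessment includes new lesions, and nadir is the lowest SPD at baseline or any assessment, the nadir includes them too. This stands, and it makes the defect one of inconsistent wording. It does not remove the problem, because the overall-response definition, which assigns the category, names the index lesions explicitly.

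**A reader might infer that any patient with unchanged disease is classed as progressing.** The documents do not support that. Index shrinkage below baseline, new measurable lesions of at least 25% of the index nadir, and a second or later post-baseline assessment are all needed.

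**A reader might infer that responders are lost from irORR.** That is not shown. The overall-response definition lets response relative to baseline be recorded even after confirmed irPD, absent other anticancer therapy, and Section 6.4.3.4 takes the best response over all available assessments. In the 30 + 15 case the scan that meets irPD also confirms irPR, and no rule cancels it. For stable patients Section 6.4.3.4 is less clear, since a best response of irSD requires absence of irPD as best response. An irDCR effect is possible but not established.

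**A reader might infer that Table 6.4.1.6 contradicts the text.** With baseline 100, regrowth from 40 to 60 is +50% over nadir (irPD by the text) but -40% from baseline, which would be irSD if the table's +25% were measured from baseline. The table does not say so, and the index-lesion definitions tie -50% to baseline and +25% to nadir. The table is incomplete, not contradictory.

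**Importance.** The primary endpoint is MTD and safety, and Section 8.4.3 gives the efficacy endpoints an explorative intent. The last scheduled doses are in Weeks 9 and 10, before the second scheduled assessment. These facts lower the priority but do not correct the dates.

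**Conclusion.** The point holds within limits. Followed as written, the second irPD criterion can assign progression to unchanged or even shrinking disease when the three conditions above are met. The firm consequences are false event dates for irPFS and irDoR. irDCR may be affected, an irORR effect is not established, and the MTD endpoint is untouched.

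The size per patient is shown by the illustrative cases: +33.3% or +50.0% on the written rule against 0% like for like. How many patients would be affected cannot be derived, because the documents do not say how often new lesions accompany index shrinkage. With at most 19 patients, each one affected is at least 1/19 = 5.3% of the sample.

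The conclusion rests on the index-only reading of nadir. On the looser reading the false irPD disappears, but the same scans then get different categories depending on which paragraph the assessor follows. Either way the text should be fixed, though it does not threaten the primary objective.

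**What to change.** Reconcile the SPD calculation paragraph, Section 6.4.3.3 and Table 6.4.1.6 for the derivation of the irRC endpoints:

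1. Let nadir and current burden contain the same lesions: current irSPD against the lowest earlier irSPD, with baseline included. Use one wording throughout.
2. Say whether the index-only irPD criterion remains alongside it.
3. State in Table 6.4.1.6 that -50% is measured against baseline and +25% against nadir, as the index-lesion definitions indicate.
4. State which category prevails when irPR and irPD are both met at one assessment. A like-for-like nadir does not remove the need: with baseline 100, nadir irSPD 20 and current irSPD 30, the change is 30/100 - 1 = -70% (irPR) and 30/20 - 1 = +50% (irPD).

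irPD also bears on stopping treatment (Sections 4.1.6 and 4.2.3), and Section 6.4.3.3 says that irRC guides care. For that use the sponsor must reconcile the passages; no clinical rule is proposed here.

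The cost is wording and endpoint derivation. The lesion measurements are already collected.

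### The second overall irPD criterion compares index plus new lesions with an index-only nadir, so an unchanged scan can be called progression when new lesions reach 25% of that nadir

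*Combined protocol and SAP*

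**What the plan says.** Under the overall-response definitions in Section 6.4.3.3, two criteria for irPD are listed and either is enough: "Any of the following will constitute progressive disease".

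- First criterion: "At least 25% increase in the SPD of all index lesions over nadir SPD calculated for these lesions". Both sides cover index lesions.
- Second criterion, with the same 25% threshold, applied to the "increase in the SPD of all index lesions and new measurable lesions (irSPD) over the nadir SPD calculated for the index lesions". The numerator covers index plus new measurable lesions; the reference covers index lesions only.

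The other definitions do not agree on which lesions the nadir covers.

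- *Calculation of Sum of Product of Diameters*: "The SPD is calculated as the sum of the product of the diameters for index tumor lesions". The nadir is the lowest SPD at baseline or at an assessment, and it classifies later assessments.
- *Non-index lesions*: progression is tied to the point at which "the SPD at nadir of the index lesions increases by the required amount".
- Opening of 6.4.3.3: "The SPD at TA using the irRC for progressive disease incorporates the contribution of new measurable lesions".
- *Index lesions*: irPD is judged by "taking sum of the products of all index lesions and any new lesions) when compared to SPD at nadir". Whether that nadir includes new lesions is not stated.
- *Impact of new lesions*: new lesions by themselves are not progression; they enter through total burden.
- Table 6.4.1.6 classifies by percent change including new measurable lesions but names no reference point.

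irPR is judged against baseline: "A decrease, relative to baseline of the irSPD of 50% or greater is considered an irPR". By Sections 8.3.2.1 and 8.3.2.2, irPD ends irDoR and is an irPFS event.

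**The concern.** A percent change is interpretable only if both sides measure the same lesions. Under the second criterion, the whole area of a new lesion counts as growth at every later scan, even when that lesion was there when total burden was at its lowest and nothing has grown since. A confirmatory scan does not protect the patient, because the same mismatch recurs.

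Section 1.3.6.2 lists response despite new lesions among the recognised response patterns with ipilimumab, and the immune-related criteria are used here so that such patients are not called progressors too early. The criterion as written works against that aim. It also lets two analysts, each following a different paragraph, derive different irPFS and irDoR dates from the same measurements. The study has at most 19 patients, so each such patient carries weight in a Kaplan-Meier median.

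**Working it through.** The documents give no figure to reproduce. I applied the written rules to hypothetical patients; the lesion sizes are my assumptions.

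**Inputs from the plan.** irPR: irSPD at or below 50% of baseline. irPD, first criterion: index SPD at least 1.25 times the index nadir. irPD, second criterion: irSPD at least 1.25 times the index nadir. The nadir comes from earlier assessments. Scans fall at Weeks 12, 18 and 24 (Section 4.1.2).

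**When unchanged disease triggers irPD.** Let I be index SPD at its nadir and N the area of new measurable lesions. The second criterion gives (I + N)/I − 1 = N/I, so it is met when N is at least 0.25 × I. With no new lesions the change is 0%. With I = 40 and N = 8 it is 8/40 = +20%, which is not irPD.

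**Example 1, stable disease.** Baseline 20; index 10 plus new 3 = 13 at Weeks 12, 18 and 24.

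- Week 12 against baseline: 13/20 − 1 = −35%, irSD.
- Week 18, first criterion: 10/10 − 1 = 0%.
- Week 18, second criterion: 13/10 − 1 = +30%, irPD.
- Week 18, like-for-like (lowest prior irSPD, 13): 13/13 − 1 = 0%, not irPD.
- Week 24 repeats Week 18 and confirms irPD under the literal rule.

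**Example 2, response.** Baseline 20; index 7 plus new 2.5 = 9.5 at Weeks 12 and 18.

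- Week 12: 9.5/20 − 1 = −52.5%, irPR; the identical Week 18 scan confirms it.
- Week 18, second criterion: 9.5/7 − 1 = +35.7%, irPD. Like-for-like: 0%.
- irDoR runs from the first response assessment, so irPD dated at Week 18 gives 18 − 12 = 6 weeks. With a like-for-like reference the response is continuing.

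**Real growth is still caught.** If index nadir is 30 with no new lesions and a new lesion of 10 then appears, (30 + 10)/30 − 1 = +33.3% under either reference. With index unchanged at a baseline of 100 and new lesions of 30, both give +30%.

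**Frequency.** The documents do not say how often new lesions occur or how large they are. For illustration I drew Week 12 index SPD from a log-normal distribution and new-lesion area from a uniform distribution, both as fractions of baseline. I kept patients without irPD at Week 12 and repeated the same scan at Week 18.

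| Index median | Log-SD | New-lesion area | irPD at Week 18, as written | Like-for-like |
|---|---|---|---|---|
| 0.8 | 0.5 | 3–40% | 59% | 0% |
| 0.8 | 0.5 | 3–20% | 23% | 0% |
| 0.8 | 0.5 | 3–10% | 3% | 0% |
| 1.0 | 0.3 | 3–15% | 0.9% | 0% |
| 0.5 | 0.5 | 3–40% | 73% | 0% |

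These are shares of patients who have new lesions, not of all patients.

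**The case against.** The best defence is that the plan, read as a whole, already includes new lesions in the nadir. Section 6.4.3.3 opens by putting new measurable lesions into the SPD at each assessment for progression, and the nadir is the lowest such SPD. A programmer who follows those two statements obtains the like-for-like rule. This stands in part: the fault is a contradiction, and bias follows only if the second criterion is applied as worded. But that criterion names the index lesions expressly, and the non-index paragraph does too, so the literal reading is the natural one. Table 6.4.1.6 does not settle it: read against baseline it gives irSD in Example 1 and irPR in Example 2, but it states no reference.

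A reader might infer several stronger claims that the documents do not support.

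- *Any patient with unchanged disease is called progressing.* Only those meeting the 25% condition are.
- *Even shrinking disease is called irPD.* Not necessarily. If irSPD falls 60, 48, 36 with index 40, 32, 24, the second criterion gives 48/40 = +20% and then 36/32 = +12.5%, because the nadir comes from earlier scans.
- *Meeting irPR and irPD at one scan proves the error.* It does not. In the clean-nadir case above, with baseline 100, the later scan is −60% from baseline and +33.3% from nadir under either reference.
- *Best response is corrupted.* Response may be recorded after confirmed irPD, and irBOR takes the best response over the study, so irORR is largely protected. Example 1 already has irSD at Week 12; loss from irDCR is possible but not shown.
- *Most patients with new lesions are affected.* The 59% depends on assumed lesion sizes.

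The affected endpoints are also secondary and exploratory in intent (Section 8.4.3).

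**Conclusion.** The concern holds in conditional form. The second irPD criterion uses mismatched lesion sets and conflicts with the paragraphs that describe total burden. Applied literally, it creates false irPFS events and shortens irDoR in patients whose existing new measurable lesions total at least 25% of the index nadir while index lesions are at that nadir. Per patient the effect can be decisive: an irPD call on zero change, repeated at confirmation. Across the trial the size is unknown, since the illustrative span of about 1% to 73% among patients with new lesions reflects assumptions and not trial data. The MTD and safety conclusions do not depend on it. The point deserves correction because the endpoints are planned secondary analyses and the definition decides event dates.

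**What to change.** Reconcile the definitions from *Calculation of Sum of Product of Diameters* through Table 6.4.1.6 on which lesions the nadir includes, and give the table a reference point. For deriving irPFS, irDoR and irBOR, have the second criterion compare irSPD with the lowest prior irSPD, baseline included. Leave the first, index-against-index criterion as it stands. State which category prevails when irPR and irPD are both met at one scan.

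The drafting cost is a few sentences and a small change to the derivation, using the index and new-lesion measurements that irSPD already requires. Settle it before scans are read. Section 4.1.1 stops tumour assessments after irPD, so images following a wrongly called irPD may not exist, and later re-derivation cannot then recover the true event date. If scans have already been classified, re-derive from lesion-level data and list the patients whose imaging ended on the second criterion alone. irPD also bears on treatment and further scanning elsewhere in the protocol; any consequence there is for the sponsor to reconcile.
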